### Adverse events

Any expected or unexpected adverse events will be reported by the participants and practitioners at every visit and followed up to completion. The adverse events known to be related to auricular acupuncture treatment include local bleeding or pain at the needle insertion points, local redness, itching, and dizziness during treatment and the follow-up period [17]. If any adverse events occur, the patient will be provided appropriate treatment. Serious adverse events will be reported to the principal investigator immediately, and the patient will be withdrawn from the clinical trial; details, including the date of occurrence, lost time, measures taken related to the treatment, causal relationship with the treatment, and treatment of the adverse event, will be recorded.

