**Methods/designs:**

This on-going study is a two parallel arm, assessor-blinded, randomised controlled trial. Sixty participants with prehypertension and stage 1 hypertension will be recruited and randomly allocated into two groups in a 1:1 ratio. Participants in the auricular acupuncture group will receive auricular acupuncture treatment two times per week for 4 weeks. Participants in the usual care group will not receive any acupuncture treatment during the study period. All participants in both groups will be provided with verbal and written educational materials regarding the dietary and physical activity habits for controlling high blood pressure, and they will self-manage their lifestyle, including diet and exercise, during the study. The primary outcome is the 24-h average systolic and diastolic blood pressure, as measured with an ambulatory monitor. The secondary outcomes are the mean change in the average systolic and diastolic blood pressure during day- and night-time, the circadian rhythm of blood pressure, the mean arterial pressure, the change in blood pressure before and after auricular acupuncture treatment, the EuroQOL-5D (EQ-5D), heart rate variability (HRV), body mass index (BMI) and laboratory examination, including lipid profile and high sensitivity C-reactive protein (hs-CRP). Safety will be assessed at every visit.

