Acupuncture has been widely used to treat various conditions, including cardiovascular disease and hypertension [8]. The mechanisms underlying the BP-lowering effect of acupuncture are associated with the control of BP modulators such as renin [9], aldosterone [10], angiotensin II [11] and endothelin-1 [12], and neurotransmitter modulation such as glutamate, GABA, serotonin and endocannabinoids [13]. Of three high-quality, randomised, controlled trials, two showed a positive effect on BP [14,15], but one trial reported a non-significant BP reduction between the groups [16]. Auricular acupuncture is one type of acupuncture based on the understanding that the external ear represents all parts of the human body, including the internal organs, and provides acupuncture points corresponding to these parts [17,18]. Several articles have evaluated the effect of auricular acupuncture on controlling BP [19-22]. Some studies also reported that the electroacupuncture treatment of auricular acupoints decreased BP in patients with hypertension [23,24]. However, the scientific evidence is insufficient [25]. Most previous studies have some methodological limitations, including low quality of the study design, small sample size, inadequate control groups, and a lack of suitable outcome measures. In addition, there is no clinical trial evaluating the effect of auricular acupuncture on prehypertension. Safe and effective interventions that are able to manage pre/mild hypertension would be desirable. Therefore, more rigorous studies are needed to elucidate the effect and safety of auricular acupuncture on pre/mild hypertension.

In the present study, we aimed to perform a randomised controlled clinical trial in patients with prehypertension and stage 1 hypertension to evaluate the effect and safety of auricular acupuncture compared with usual care. The 24-h ambulatory blood pressure will be used as the primary endpoint. The results derived from this study will also be used to explore the feasibility of auricular acupuncture treatment and calculate the appropriate sample size for a future large clinical trial.

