### Randomisation

Study participants who meet the eligibility criteria will be randomly assigned to two groups (the auricular acupuncture group or the usual care group) at the second visit through central randomisation in a 1:1 ratio. Randomisation will be conducted using a computer-generated random allocation sequence through the stratified block randomisation method of the SAS package (version 9.1.3; SAS Institute, Inc., Cary, NC, USA) by a statistician with no clinical involvement in this trial, and the patients will be stratified by centre, age (19–30, 31–40, 41–50, 51–65 years) and sex.

Allocation concealment will be ensured, as the randomisation code will be released after the participants are recruited into the trial and all baseline measures are taken. The subjects and practitioners will be aware of the allocation arm according to the routine care setting. However, the outcome assessors and the statistician performing the data analyses will be masked to the treatment allocation [26].

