Heart rate variability (HRV) is a useful non-invasive tool to investigate the sympathetic and parasympathetic function of the autonomic nervous system and cardiac autonomic dysregulation in hypertension. An SA-6000 (Medicore Co. Ltd., Seoul, Korea) will be used for studying HRV. The results, including the standard deviation of all of the normal-to-normal intervals (SDNN), the square root of the mean squared differences of successive normal-to-normal intervals (RMSSD), the percentage of successive normal interbeat intervals greater than 50 ms (pNN50), the very low frequency (VLF), low frequency (LF), high frequency (HF), total power (TP), LF/HF ratio, heart rate, and HRV index, will be analysed at baseline and 5 and 13 weeks after baseline. This test will be performed at DongGuk University Ilsan Oriental Hospital only.

BMI (body mass index) is the most commonly used indicator of obesity and is determined from height and weight. In this trial, BMI will be assessed at baseline and 5 and 13 weeks after baseline.

Laboratory examination will be performed for the lipid profile, hs-CRP, fasting blood glucose, and uric acid. The lipid profile measures total cholesterol, HDL cholesterol, LDL cholesterol, and triglyceride levels. Blood samples will be collected after overnight fasting at baseline and at weeks 5 and 13. An overview of the outcome measurement time points is presented in Table 1.

**Table 1 T1:** Schedule for treatment and outcome measurements

**Period**	**S**	**T**								**F**	
Visit	1	2	3	4	5	6	7	8	9	10	11
Week		1		2		3		4		5	13
Informed consent	●										
Inclusion/exclusion criteria	●										
Random allocation		●									
Auricular acupuncture treatment		○	○	○	○	○	○	○	○		
BP before and after auricular acupuncture treatment		○	○	○	○	○	○	○	○		
24-h ABPM	●					●				●	●
Laboratory examination		●								●	●
BMI	●					●				●	●
EQ-5D		●								●	●
Heart rate variability	●									●	●
Safety assessment		●	○	○	○	○	○	○	○	●	●

*S* Screening period, *T* treatment period, *F* follow-up period, *BP* blood pressure, *ABPM* ambulatory blood pressure monitoring, *BMI* body mass index, *EQ-5D* EuroQOL-5D.

●: Both the auricular acupuncture group and the usual care group.

○: Only the auricular acupuncture group.

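### Table 1 schedules nine safety assessments after randomisation for acupuncture and two for usual care, so early non-specific adverse events may be unequally counted

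*Protocol article*

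**What the plan says.** Two places in the article set a uniform rule. The abstract (Methods/designs) states "Safety will be assessed at every visit". The Adverse events section states "Any expected or unexpected adverse events will be reported by the participants and practitioners at every visit and followed up to completion". Neither separates the arms.

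Table 1, under Secondary outcome measurements, gives the operational schedule. Its row "Safety assessment" has a filled circle at visits 2, 10 and 11 and an open circle at visits 3 to 9. The legend defines the filled circle as "Both the auricular acupuncture group and the usual care group" and the open circle as "Only the auricular acupuncture group". Allocation takes place "at the second visit through central randomisation in a 1:1 ratio", so every visit from 3 onwards is after randomisation.

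The Background gives the aim as "to evaluate the effect and safety of auricular acupuncture compared with usual care", so safety is framed as a contrast between arms.

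**The concern.** An adverse event count reflects both how often events occur and how often patients are asked. During the four treatment weeks, acupuncture patients are asked about safety twice a week. Usual care patients have no scheduled enquiry between allocation day and week 5. Needle-site reactions are not affected, since they can arise in only one arm. Non-specific symptoms are. The Adverse events section lists dizziness among the events known to be related to the treatment, and usual care patients can report dizziness too. Attributing it to acupuncture needs comparable enquiry in the control arm. The people who report events, participants and practitioners, also know the allocation (Randomisation section).

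What is at stake is the comparative safety statement from this pilot, and the schedule that a larger trial might inherit. The primary endpoint is not affected: Table 1 places 24-h monitoring at visits 1, 6, 10 and 11 in both arms.

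**Working it through.** **1. Count from Table 1.** Randomisation is at visit 2.

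| | Acupuncture | Usual care |
|---|---|---|
| Allocation day (visit 2) | 1 | 1 |
| Visits 3 to 9 | 7 | 0 |
| Visits 10 and 11 (weeks 5 and 13) | 2 | 2 |
| Total after randomisation | 7 + 2 = **9** | 0 + 2 = **2** |
| Total including visit 2 | 10 | 3 |

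From visit 10 onwards the schedules are the same, so the imbalance lies wholly between week 1 and week 5.

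**2. Can the text and the table be reconciled?** One could read the uniform rule as each arm's own visits. Table 1 lists nothing for usual care at visits 3 to 5 and 7 to 9, so those visits would not conflict with the rule. Visit 6 (week 3) still does. Usual care has filled circles there for 24-h monitoring and BMI, but the safety mark is an open circle. If the text governs at visit 6, the count is 9 versus 3. If the table governs, it is 9 versus 2.

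**3. Possible size (illustration; the capture and risk values are assumptions).** Let p be the true risk of a non-specific event up to week 5, equal in both arms. Let c_A and c_U be the proportions of such events captured in acupuncture and in usual care.

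Apparent risk ratio = (p × c_A) / (p × c_U) = c_A / c_U, whatever p is.

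Expected patients with a reported event = 30 × p × c, with 30 per arm from the Sample size section. Taking c_A = 0.90 and p = 0.20:

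| c_U | Apparent risk ratio | Acupuncture (of 30) | Usual care (of 30) |
|---|---|---|---|
| 0.90 | 0.90/0.90 = 1.00 | 30 × 0.20 × 0.90 = 5.4 | 30 × 0.20 × 0.90 = 5.4 |
| 0.70 | 0.90/0.70 = 1.29 | 5.4 | 30 × 0.20 × 0.70 = 4.2 |
| 0.50 | 0.90/0.50 = 1.80 | 5.4 | 30 × 0.20 × 0.50 = 3.0 |
| 0.30 | 0.90/0.30 = 3.00 | 5.4 | 30 × 0.20 × 0.30 = 1.8 |

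The ratio equals 1 only if recall at visit 10 is as complete as twice-weekly enquiry.

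**4. Effect of the remedy on the count.** Restricting the contrast to shared assessments gives 2 versus 2 (visits 10 and 11). Adding visit 6 in both arms gives 3 versus 3.

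**The case against.** Most of the imbalance follows from a pragmatic design in which the control arm has no treatment sessions to attend. The Discussion concedes that the arms differ in number of visits, that this can bias results, and that interpretation will be cautious. The direct contradiction between text and table is a single cell, visit 6. The Statistical analysis section names no between-arm test of adverse events, and several of the listed related events are tied to the needle. All of this stands and limits the weight of the point. It does not remove it: the comparative aim is stated, and the Discussion equalises only the primary outcome measurements. At visit 6 the difference is also avoidable, since both arms are present.

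A reader might go further and treat each enquiry as an independent chance of finding an event. At an assumed 5% per enquiry, that gives 1 − 0.95^9 = 0.370 against 1 − 0.95^2 = 0.098, a ratio of about 3.8. The document does not support that figure. It supposes that an enquiry covering a few days yields as much as one covering several weeks, and that an event not asked about promptly is lost. Nothing in the Adverse events section limits reporting to events present on the day, and usual care is asked at week 5. Nor does the document support saying that acupuncture will look less safe. It may.

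**Conclusion.** The point holds as a contradiction between text and table, together with a possible ascertainment bias of unknown size. The count of 9 versus 2 is exact from Table 1, and visit 6 contradicts the uniform rule on any reading. The likely direction is over-counting of non-specific events up to week 5 in acupuncture relative to usual care. The size cannot be derived from the document. The range of 1.0 to 3.0 for the apparent risk ratio rests on an assumed 90% capture in acupuncture and 90% to 30% in usual care, with equal true risk.

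A reader might infer that a formal adverse-event comparison is planned and will be invalid. The document states a comparative aim but specifies no such test, so the point concerns how safety data are collected and presented. It is worth correcting because the aim is explicit and most of the remedy is a matter of wording and reporting.

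**What to change.** 1. In Table 1, mark safety assessment at visit 6 for both arms, for patients who have not yet passed that visit. Reword the abstract and the Adverse events section so that they agree with the table.
2. Base any between-arm comparison of adverse events on assessments shared by both arms: visits 10 and 11, plus visit 6 where it was collected in both. Use the same question and the same recall period, such as since the last shared assessment.
3. Report events from the acupuncture-only visits, and needle-site reactions, descriptively for the acupuncture arm.
4. State that some difference remains, because acupuncture patients will have been prompted at the intervening visits.

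**Cost.** It takes one added enquiry at a visit that usual care already attends, plus wording and a reporting rule. Fewer events will enter the comparison. The Trial status section gives 54 patients already recruited of the planned 60, so the visit 6 change may reach only some of them. Visit 6 safety data in usual care will then be incomplete, and the report should say so.

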#### Usual care group

Subjects randomised to the usual care group will not be given auricular acupuncture treatment. However, participants in both groups will be provided with verbal and written educational materials regarding dietary and physical activity habits for controlling high blood pressure and self-manage their lifestyle, including diet and exercise, during the study. Additional treatment, including antihypertensive drugs and treatment with traditional Korean medicine, will be prohibited, and any violations will be recorded.

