### Statistical analysis

All analyses will be performed with SAS (version 9.1.3; SAS Institute, Inc., Cary, NC, USA) by a statistician blinded to the allocation of groups. Statistical analysis will be undertaken on the intent-to-treat (ITT) basis with a 95% confidence interval using multiple imputations. The ITT analysis will include all patients who are randomised [32], and the per-protocol (PP) analysis will include patients who complete the study and do not have major protocol violations [33]. All analyses will be based on the ITT population, and the result of the ITT analysis will be compared with the PP analysis to assess the sensitivity.

Analysis of covariance (ANCOVA) with the baseline score as a covariate for the whole subject pool will be used to assess differences in treatment outcomes between the two groups at each of these time points as a main analysis. The results for the applicable stratified groups with centre, age, and sex as stratified variables will be assessed as additional analyses. The repeated measures analysis of variance will be performed for the different time point assessments.

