## Trial status

The trial is currently in the recruitment phase, and 54 patients were recruited.

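### Any serious adverse event, in either arm and whatever its cause, removes the patient from the trial rather than only from needling, so ambulatory blood pressure that could be measured must be imputed

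*Protocol article*

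**What the plan says.** The Adverse events section sets the rule: "Serious adverse events will be reported to the principal investigator immediately, and the patient will be withdrawn from the clinical trial". The same sentence goes on to list what is documented: "measures taken related to the treatment, causal relationship with the treatment, and treatment of the adverse event, will be recorded". Causality is therefore noted but does not decide whether the patient leaves. The section also says that adverse events are followed to completion.

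Four other places bear on the rule:

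- **Usual care group:** "Subjects randomised to the usual care group will not be given auricular acupuncture treatment". For antihypertensive drugs and traditional Korean medicine in this group, the text says that they "will be prohibited, and any violations will be recorded".
- **Table 1 (Secondary outcome measurements):** 24-h ABPM is marked at screening and at visits 6, 10 and 11 (weeks 3, 5 and 13) with the symbol for "Both the auricular acupuncture group and the usual care group". Safety assessment carries that symbol at visits 2, 10 and 11; at the other treatment visits it applies to the acupuncture group only.
- **Statistical analysis, missing data:** "Statistical analysis will be undertaken on the intent-to-treat (ITT) basis with a 95% confidence interval using multiple imputations". All randomised patients are included.
- **Statistical analysis, sensitivity:** the intention-to-treat result is compared with a per-protocol result, where "the per-protocol (PP) analysis will include patients who complete the study and do not have major protocol violations".

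**The concern.** Stopping a treatment and leaving a study are different decisions, and the rule merges them. After a serious event there may be good reason to stop needling. There is seldom a reason to stop measuring blood pressure in a patient who is able and willing to attend. In usual care the rule stops no study treatment at all; its only effect is to end observation.

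At stake is missing primary-outcome data created by the protocol itself. Some of it may be informative. If the event is related to blood pressure, the unobserved values could be higher than imputed, or lower if antihypertensive treatment was started. Many serious events in this population would have nothing to do with blood pressure, so the missingness need not be informative and the direction of any bias is unknown. Either way, the estimate for these patients rests on an imputation assumption that the trial's data cannot test.

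**Working it through.** The article gives no figure on this point to reproduce: no serious-event rate, and no SD or power calculation behind the 30 per group. The check has two parts.

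**Reading the text**

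1. The rule is mandatory, it refers to the trial and not to the treatment, and it has no limit by arm or cause.
2. No section provides for outcome assessment after withdrawal.
3. Table 1 places up to three post-baseline ABPM recordings per patient, in both arms, at risk.
4. Withdrawn patients stay in the intention-to-treat set, so their missing values are imputed. They do not complete the study, so they are absent from the per-protocol set. Comparing the two sets shows how far the estimate moves between them; it cannot show whether the imputed values were right.

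**Size**

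Inputs from the article: 60 patients, 30 per arm (Sample size); three post-baseline ABPM recordings (Table 1), so 3 × 60 = 180 in all; completion by more than 80% of those randomised (Sample size).

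Assumed inputs: serious-event risk p of 1–3% over 13 weeks; imputation error of 10–20 mmHg for one patient; SD of 24-h blood pressure of 8–12 mmHg.

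- **Expected withdrawals**, 60p: 60 × 0.01 = 0.6; 60 × 0.03 = 1.8.
- **Chance of at least one**, 1 − (1 − p)^60: 1 − 0.99^60 = 0.45; 1 − 0.97^60 = 0.84.
- **Wider range of p**: at 0.5%, 0.3 patients and a chance of 0.26; at 5%, 3.0 patients and a chance of 0.95.
- **Recordings lost, upper bound** (every event before visit 6): 3 × 0.6 = 1.8 to 3 × 1.8 = 5.4 of 180.
- **Recordings lost, events spread evenly over weeks 1 to 13**: 2/12 of events fall before week 3, 2/12 between weeks 3 and 5, and 8/12 later. Mean loss per event is (2×3 + 2×2 + 8×1)/12 = 1.5, giving 1.5 × 0.6 = 0.9 to 1.5 × 1.8 = 2.7 of 180.
- **Chance that any patient loses the week-5 reading**, same even spread (one third of events fall before week 5): 1 − (1 − 0.01/3)^60 = 0.18; 1 − (1 − 0.03/3)^60 = 0.45.
- **Shift of an arm mean from one patient**: 10/30 = 0.33; 20/30 = 0.67 mmHg.
- **Standard error of the difference**, SD × √(2/30): 8 × 0.258 = 2.07; 12 × 0.258 = 3.10 mmHg.
- **Shift relative to the standard error**: 0.33/3.10 = 0.11 to 0.67/2.07 = 0.32.
- **Completion target**: 48/60 is exactly 80%, so at least 49 completers are needed and 12 losses break the target. P(X ≥ 12 | n = 60, p = 0.03) = 1.9 × 10⁻⁷, about 2 in 10 million.

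**The case against.** The strongest reply is that the harm is inferred. The article says that the patient is withdrawn; it does not say in so many words that no further outcomes are taken, and a journal article may leave early-termination procedures to the full protocol. That deserves some weight. But the finding rests on a rule that is stated, not on a missing detail. Withdrawal from the trial ordinarily means the end of scheduled assessment, and reading it as treatment only has no meaning in usual care. If treatment only was intended, the wording needs the same correction.

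Several points on size stand:

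- The eligibility criteria exclude cardiovascular, cerebrovascular, renal and hepatic disease, cancer and medicated diabetes, in adults aged 19 to 65, so events should be few.
- Under an even spread, two thirds of events would cost only the week-13 reading.
- The upper ratio of 0.32 pairs a 20 mmHg error with an SD of 8, a miss of 20/8 = 2.5 SDs.
- The event itself is still followed to completion, so the safety loss is limited to later scheduled assessments; for usual care these are visits 10 and 11 only.

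Blood pressure after a serious event may also reflect hospital care or drugs that the trial prohibits. That affects how the values are interpreted. It is a reason to record the drug, and an intention-to-treat comparison is still better served by measured values than by imputed ones.

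Finally, no per-protocol comparison can validate imputation for any kind of dropout. That is true, but here the dropout is imposed by the protocol and can be avoided.

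**Conclusion.** The concern holds and is minor. The rule as written turns a serious event into loss of the primary outcome with no regard to arm or cause, and the analysis then has to impute what could often have been measured. In this pilot, one or two patients at most would be expected to be affected under the assumed 1–3% risk, with a shift of 0.11 to 0.32 standard errors per patient in an unknown direction. That would not by itself change the trial's conclusions or breach the completion target. The figures depend on the assumed event risk, imputation error and SD, none of which the article supplies; the reading of the rule does not. The rule matters more for the planned large trial, where at the same risk the number of patients lost grows in proportion to enrolment.

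**What to change.** Replace the withdrawal clause in the Adverse events section with a rule on these lines:

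- After a serious adverse event, the investigator decides whether auricular acupuncture stops.
- Unless consent is withdrawn, the patient stays in the trial for the remaining assessments where feasible: ABPM at visits 6, 10 and 11, and the safety assessments that Table 1 schedules for that arm.
- These data are used in the intention-to-treat analysis.
- Any antihypertensive drug started after the event is recorded, as is already done for violations of the treatment ban.

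The same rule should go into the protocol of the later large trial.

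The cost is a short amendment at the two institutional review boards and some follow-up effort at visits already scheduled. The benefit to this trial is limited by its stage: "The trial is currently in the recruitment phase, and 54 patients were recruited". The change can help only patients still in treatment or follow-up and those yet to enter.
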